**II. How effective is the application of SML to enhance recruitment for clinical trials among Twitter users in LA County?**

- a. How does the enrollment rate that results from SML on Twitter compare to historic recruitment data? Measured actual versus projected accrual per month at USC Norris.

## 3. STUDY PROTOCOL

### 3.1 Protocol title

The use of social media listening for targeted recruitment of Twitter users in LA County in cancer trials compared to historic recruitment data: A mixed-methods study.

### 3.2 Protocol version number and date

Version 5, Jan 23, 2018.

### 3.3 Study design

#### 3.3.1 General study design

We will use a mixed-methods interrupted time series study design with a before and after intervention at the USC Norris Comprehensive Cancer Center (USC Norris). This study will examine the feasibility and gain preliminary data on the impact of targeted social media listening (SML) as a tool for enhancing recruitment to cancer trials (non-small cell lung cancer, colon cancer, breast cancer, prostate cancer, kidney cancer, lymphoma) among Twitter users in LA County. Disease categories will be randomized and rolled in consecutively, one every two weeks in the first quarter. The order will be randomized.

We aim to recruit all interventional trials in the select disease areas (84; based on USC Norris data from 1/1/2017 to 07/07/2017) open for recruitment to accrual for treatment of patients with non-small cell lung cancer, prostate cancer, breast cancer, colon cancer, kidney cancer, or lymphoma) at USC Norris. We may include another tumor type if the number of trials is insufficient or other tumor types and Twitter user activity emerge that are of interest to the research question. Disease categories will be randomized and rolled in consecutively, one every two weeks in the first quarter. Once a study is enrolled it stays on for the period of this study. Each trial will be exposed to the intervention for 9 months. This design was chosen to fit within the triage protocol of USC Norris and cause minimal disruption to the staff. Success will be compared to historical success achieved without the use of SML.

Outcomes will be the feasibility of the study described by the acceptance of and satisfaction with SM recruitment method among USC Norris study team members and Twitter users in LA County and by describing the proportion of eligible cancer trials to be enrolled in the study, cancer disease types and studies that can be monitored at a time, eligible participants that can be enrolled, diversity of participants, staffing required to monitor eligible studies, burden of recruitment/cost of intervention.

- Post-qualitative interviews with study team members will be undertaken to explore trial participants' views and experiences of the trial methods and intervention (principal investigators, clinical research coordinators, recruitment specialists). The interview guide is under development and will be submitted to the USC HSCIRB for review. Qualitative research expert [name] (consultant on this project) will advise this part of the study. We will gather a range of data. Please see **Table 3** that lists all outcomes in the *Data analysis* section 3.3.7.

Recruitment of USC Norris clinical trial team members: As we enroll cancer clinical trials in this study, the study co-PI ([name]) will contact the cancer trial PI via email (using USC's email system) to invite the PI and one additional study member (e.g., clinical research coordinator, recruitment specialist) to participate in an interview.

- Brief survey interviews with contacted Twitter users will be conducted by the study teams with prospective study participants who contacted the study team in response to SM recruitment. The goal of the survey is to collect demographic information about the prospective study participants and to better understand their perception of the SM recruitment method used. Qualitative research expert [name] (consultant on this project) will also advise this part of the study. (See **Appendix 6** for the full questionnaire)

Additionally, we will look at the impact of the SM intervention measured by monthly observed recruitment rate vs. monthly projected accrual target. We will calculate the effect size estimate of the number of people to enroll cancer trials as a result of targeted social media listening and recruitment (SML) via Twitter.

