| Objectives                             | 
 
1. Examine the feasibility (acceptance among USC Norris study team members and Twitter users in LA County) of targeted social media listening (SML) via Twitter as a tool for enhancing recruitment to cancer trials.
 
2. Gain preliminary data on the impact (i.e., numbers recruited versus projected accrual per trial disease area compared to historic recruitment) of targeted social media listening (SML) as a tool for enhancing recruitment to cancer trials among Twitter users in LA County. We will further estimate the effect size of the number of people enrolled per trial disease area associated with the use of targeted social media listening (SML) via Twitter.
 
                                                                                                                                                                                                                                                                                                                                                                                                                                                            |
| Number of trials/research participants | 
 
1. 84 clinical cancer trials (all interventional trials open for recruitment to accrual for treatment of patients with non-small cell lung cancer, prostate cancer, breast cancer, colon cancer, kidney cancer, or lymphoma-- based on USC Norris data from 1/1/2017 to 07/07/2017). We may include another tumor type if the number of trials is insufficient or other tumor types and Twitter user activity emerge that are of interest to the research question.)
 
2. 160 participants (2 members per enrolled trial, PIs, study coordinators, recruitments specialists)
 
                                                                                                                                                                                                                                                                                                                                                                                                                                                                                                                                                                        |

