| Primary outcomes                                      | 1. Feasibility : Acceptance of and satisfaction with SM recruitment method among USC Norris study team members and Twitter users in LA County, number of cancer trials eligible to be enrolled in study, number of cancer disease types and studies that can be monitored for on Twitter simultaneously by the SC CTSI study team, time and effort it takes the SC CTSI and USC Norris team members to respond to the resulting inquiries and decide whether or not to bring the patient in for screening, eligibility rate of prospective participants, demographic and ethnic diversity rate of those who consented/enrolled, social media message click rate, website contact form usage rate.
2. Impact : Monthly observed recruitment rate vs. monthly projected accrual target by trial disease group compared to historic data. Effect size estimate of the number of people to enroll cancer trials as a result of targeted social media listening and recruitment (SML) via Twitter.                                                                                                                                                                                                                                                                                                                                                                                                                                                                                                                                                                                            |

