## 1.3 Study objectives

1.3.1 Examine the feasibility (acceptance among USC Norris study team members and Twitter users in LA County) of targeted social media listening (SML) via Twitter as a tool for enhancing recruitment to cancer trials.

1.3.2 Gain preliminary data on the impact (i.e., numbers recruited versus projected accrual compared to historic recruitment) of targeted social media listening (SML) as a tool for enhancing recruitment to cancer trials among Twitter users in LA County. Estimate the effect size of the number of people enrolled associated with the use of targeted social media listening (SML) via Twitter as a tool for enhancing recruitment to cancer trials.

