**Figure 1. Study flow diagram of study design, procedures and stages for intervention A.**

## PARTICIPANTS

General characteristics of the proposed participant population(s): Any Twitter user who mentions one or more of the pre-selected cancer disease topics will be contacted via Twitter.

Anticipated number of research participants: We anticipate increasing the number of participants enrolled per trial and per month based on the following historic data from the past five years (see **Appendix 2**):

- Non-small cell lung cancer: Minimum of 2 participants per month
- Colon cancer: Minimum of 2 participants per month
- Prostate cancer: Minimum of 3 participants per month
- Breast cancer: Minimum of 2 participants per month
- Kidney cancer: Minimum of 1 participants per month
- Lymphoma: Minimum of 1 participants per month

Inclusion criteria for prospective trial participants: We will include all prospective trial participants in this study that come from Twitter in response of our SM recruitment interventions, provided they meet the specific trial's eligibility criteria.

Exclusion criteria for prospective trial participants: Persons who do not meet the eligibility criteria of any of the trials open to accrual will be excluded from participation, and persons who may be eligible (e.g., disease/histology, stage, prior treatment) but do not meet additional trial-specific requirements such as insurance or allergy to drug). These may vary by clinical trial. We will count these people as engaged but not enrolled and document the specific reasons.

Screening procedures: We will use the eligibility criteria as outlined above to verify clinical eligibility for participation in the study.

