| Contact data      | contact_message      | Text             | Content of contact message                                      |                                                                                                                                        |            |
| Contact data      | date_sent            | Numeric          | Date of contact message                                         |                                                                                                                                        | mm/dd/yyyy |
| Contact data      | sol_acknowledgement  | Numeric          | Contact acknowledged solicitation                               | 1=yes 0=no                                                                                                                             |            |
| Contact data      | date_acknowledgement | Numeric          | Date contact acknowledged solicitation                          |                                                                                                                                        | mm/dd/yyyy |
| Contact data      | patient              | Numeric          | Is the contacted person a cancer patient?                       | 1=yes 0=no                                                                                                                             |            |
| Contact data      | patient_cancer_type  | Text             | Type of cancer contact was diagnosed with                       | 1=non-small cell lung cancer
2=colon cancer 3=breast cancer 4=prostate cancer
5=kidney cancer 6=lymphoma
7=Other              |            |
| Contact data      | eligibility          | Numeric          | Is the contacted person eligible for one of the trials?         | 1=yes 0=no                                                                                                                             |            |
| Contact data      | first_name           | Text             | Contact's first name                                            |                                                                                                                                        |            |

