| Contact data | value                 | Numeric | How helpful would you say is it when research institutions reach out directly to potential clinical trial participants via Twitter?                                          | 1=Very helpful 2=Helpful
3=Somewhat helpful 4=Not helpful at all 5=Don't know                                                                                                                                                                                                                                                                                    |                                                                                                |
| Contact data | concern               | Numeric | How concerned are you about researchers and research institutions monitoring Twitter conversations to identify and contact potential study participants for clinical trials? | 1=Very concerned
2=Somewhat concerned
3=Not too concerned 4=Not concerned at all 5=Don't know                                                                                                                                                                                                                                                                 |                                                                                                |
| Contact data | contact_form_use      | Numeric | Contact used contact form on clinical trial web page                                                                                                                         | 1=yes 0=no                                                                                                                                                                                                                                                                                                                                                          |                                                                                                |

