## APPENDIX 6. QUESTIONNAIRE FOR PROSPECTIVE STUDY PARTICIPANTS

(i.e., those who contacted the study team in response to the SM recruitment)

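### Acceptance is an objective for LA County Twitter users but is measured only in those who contacted or spoke with the study team, so it cannot be estimated for the stated population

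*Protocol*

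**What the plan says.** **Target.** Protocol section 1.3 sets the first objective: "Examine the feasibility (acceptance among USC Norris study team members and Twitter users in LA County) of targeted social media listening (SML) via Twitter". The Synopsis makes the corresponding primary outcome "Acceptance of and satisfaction with SM recruitment method among USC Norris study team members and Twitter users in LA County".

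**Who is exposed.** Section 3.3.3, under Participants: "Any Twitter user who mentions one or more of the pre-selected cancer disease topics will be contacted via Twitter".

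**Who is asked.** Section 3.3.1 gives the brief survey to "prospective study participants who contacted the study team in response to SM recruitment". Appendix 6 describes its respondents in the same way, as "those who contacted the study team in response to the SM recruitment". Two items in it ask users for an attitude to the method. One asks how helpful direct outreach is. The other, listed also in Appendix 5, begins "How concerned are you about researchers and research institutions monitoring Twitter conversations".

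**How it is summarised.** In Table 3 (section 3.3.7), the user part of the acceptance and satisfaction percentage divides enrolled trial participants who are satisfied by all people engaged, defined as those who spoke with the study team.

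**What is recorded for the others.** Table 3 also has clicks per impression and enrolment per person contacted. Section 3.3.7 adds counts of contacts solicited and of contacts who acknowledge. Appendix 5 holds a yes/no flag per contact, "Contact acknowledged solicitation", and counts of replies and likes per message.

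**The concern.** The population in the objective and the population that supplies the acceptance data differ, and the step between them is self-selection on interest. A user reaches the questionnaire only by choosing to contact the team after an unsolicited public message. Users who disliked being monitored or messaged are the least likely to take that step. Section 5.2 (Table 4) itself recognises that people who post publicly may not have expected researchers to use what they post.

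Widespread objection among contacted users could therefore leave both the survey result and the Table 3 percentage unchanged. Acceptance is the first objective, and Table 4 says the preliminary data are meant to support a larger grant proposal. A statement about LA County Twitter users drawn from these data would lack a basis.

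**Working it through.** The protocol states no expected response share, acceptance rate or sample size for this outcome, so there is no figure to reproduce. The check has three parts.

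**1. Populations side by side**

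| Item | Population | Place |
|---|---|---|
| Objective 1 and primary outcome | LA County Twitter users | 1.3; Synopsis |
| Users messaged | all who mention a listed topic | 3.3.3 |
| Helpfulness and concern items | users who contacted the team | 3.3.1; Appendix 6 |
| Table 3 satisfaction, denominator | users who spoke with the team | 3.3.7 |
| Table 3 satisfaction, numerator | enrolled and satisfied users | 3.3.7 |
| Click rate | all message impressions | 3.3.7 |
| Enrolment rate | users contacted on Twitter | 3.3.7 |
| Acknowledgement flag | each contact | Appendix 5 |

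The last three rows include users who did not respond, but they record behaviour. None belongs to the acceptance and satisfaction percentage. The acknowledgement flag is yes/no, so it cannot show whether an acknowledgement was friendly or hostile. The reply and like fields count events per message. No field in Appendix 5 holds the addressee's reply or codes an objection or a request to stop.

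**2. What the survey can say about all contacted users (illustration; every rate is assumed)**

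Let r be the share of contacted users who reach the survey, a the share of those who are favourable, and n the unknown favourable share among the rest.

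Acceptance among all contacted = r × a + (1 − r) × n.

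With n unobserved, the bounds are r × a (n = 0) and r × a + (1 − r) (n = 1). For a = 80%:

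- r = 1%: 0.01 × 0.80 = 0.8%; 0.8% + 99% = 99.8%
- r = 5%: 0.05 × 0.80 = 4%; 4% + 95% = 99%
- r = 10%: 0.10 × 0.80 = 8%; 8% + 90% = 98%

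The width is 1 − r whatever a is, so at r of 10% or less it is at least 90 percentage points. If n is below a, the survey figure is too high for all contacted users. With r = 5%, a = 80% and n = 20%, the value is 4% + 0.95 × 20% = 23%.

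**3. What the Table 3 ratio can say**

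Let e be the enrolled share of those who spoke with the team, and s the satisfied share of those enrolled. The ratio is e × s and cannot exceed e.

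- e = 10%, s = 90%: 9%
- e = 20%, s = 80%: 16%
- e = 50%, s = 80%: 40%

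Set against the illustrative 23% from part 2, the first two readings are too low and the third too high. The ratio has no fixed direction as a measure of acceptance among contacted users.

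A related gap: the Appendix 6 questionnaire asks about helpfulness and concern but has no item on satisfaction, which is what the Table 3 numerator needs.

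**The case against.** The restriction is openly stated. Sections 3.3.1, 3.3.7 and Appendix 6 all say who is surveyed or counted, and research question I.g in section 2.2 asks about the satisfaction of prospective participants, which suits the surveyed group. This is a descriptive pilot with no acceptance threshold or decision rule. The bounds rest on assumed rates and would follow for any survey with that response share. All of this is true. It limits the consequence, but the objective and the primary outcome still name the wider population. A later analysis plan could not recover opinions that were never collected.

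A reader might infer more than the text supports, in four ways:

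- **That non-responders are not counted at all.** They enter click rate, acknowledgement and enrolment per person contacted. They are missing only from the acceptance outcome.
- **That acceptance is overstated.** For the helpfulness and concern items this is the likely direction, but no figure in the protocol establishes it. The Table 3 ratio can read low, because satisfied users who did not enrol are left out of its numerator.
- **That the plan would report a figure such as 80%.** Nothing in the protocol gives that figure, and an 80% favourable survey does not produce 80% under the Table 3 definition.
- **That the reply and like fields already allow each user to be classified.** They are counts per message. The messages are public, so a reply or like need not come from the person addressed.

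It can also be said that a click or a like is not acceptance of being monitored, and that silence mixes objection, indifference and messages never seen. That is correct, and any reporting over all contacted users has to respect it.

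**Conclusion.** The mismatch stands. As the protocol is written, acceptance among LA County Twitter users cannot be estimated: the survey and the Table 3 percentage describe users who came forward, and objection among the other contacted users could not alter either result. The survey items probably lean favourable, on the assumption that users who did not come forward are less accepting than those who did. The Table 3 ratio may lean either way.

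The size of any bias is unknown because the protocol gives no response share. The 80% figure and the bounds only show that a small response share leaves the wider population's acceptance almost unconstrained. The documents do not support the firmer conclusion that reported acceptance will be too high.

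**What to change.** 1. State the survey results and the Table 3 user satisfaction percentage as applying to users who engaged with the team, and word Objective 1 and the primary outcome to match. Note the enrolled-only numerator wherever the Table 3 figure is given.
2. Beside them, report with all contacted users as the denominator the proportions who acknowledged without objecting, who objected or asked to stop, and who did not respond. Treat non-response as unknown, neither acceptance nor rejection.
3. Add one per-contact field to Appendix 5 that codes the addressee's own reply as positive/neutral or as negative/request to stop. The existing reply and like counts cannot serve this purpose.

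Most of what step 2 needs is already planned: section 3.3.7 counts contacts solicited and acknowledging, Appendix 5 has the acknowledgement flag, and section 3.3.4 tags messages so that recruitment results can be traced by individual and message. The added cost is a small amount of reply capture, attribution to the addressee and coding. No further contact with users is needed. The price is a narrower, and possibly less favourable, statement about acceptance.
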